### Plans to promote participant retention and complete follow-up {18b}

The P.I. will promote participant retention and complete follow-up by daily checking with the clinical staff for new eligible patients, assuring protocol adherence and complete follow-up during the ICU and hospital stays of enrolled patients.

### Data management {19}

Patient identification will be coded and pseudo-anonymized in a list kept confidential by the P.I. up to 1 year after publication of trial results, after which it will be destroyed.

Data will be collected into a database (IBM Corp. Released 2020. IBM SPSS Statistics for Windows, Version 27.0. Armonk, NY: IBM Corp), located in a secure institutional space, accessible only through specific ID and passwords, restricted to the P.I. and associated investigators.

The P.I. will be responsible for collected data quality and the database safeguard for a period of 10 years after patient enrollment is complete.

### Confidentiality {27}

The coded list will be used for patient confidentiality and pseudo-anonymization, and to allow for quality control, while managing and analyzing the database. It will be kept in a secure institutional space, accessible only through specific ID and passwords.

### Plans for collection, laboratory evaluation, and storage of biological specimens for genetic or molecular analysis in this trial/future use {33}

This trial does not include any collection of biological specimens for genetic or molecular analysis.

## Statistical methods

### Statistical methods for primary and secondary outcomes {20a}

For the descriptive analysis, quantitative variables will be reported as means and standard deviations or as medians and interquartile ranges (*P*_25_-*P*_75_), as appropriate, and categorical variables reported as frequencies and percentages.

Quantitative variables will be analyzed using the assessment day value (D7), the daily mean value, and their maximum or minimum values. Mann–Whitney *U* test will be used to compare study groups, assuming a non-normal distribution, or two independent sample *t*-test, in case of normal distribution. Dichotomous categorical variables will be analyzed using chi-square or Fisher’s exact tests. Using daily values, mixed effects regression models will be used to consider the autocorrelation structure between the longitudinal measurements. Regarding stage 3 AKI as secondary outcome, odds ratios and corresponding 95% confidence intervals will be estimated using logistic regression models. For the study of RRT-free days, competing risks survival models will be applied considering death as the competing risk. Regarding time until death, joint survival regression models will be used to take into consideration the association of longitudinal markers with time until death. For LOS, linear regression models will be applied. For all regression studies, univariable and multivariable analyses will be performed to account for potential confounders. The absolute risk of paracentesis-related complications will be reported for both trial groups. A level of significance *α*= 0.05 will be considered. Data will be analyzed using the R Statistical Software [41].

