### Outcomes {12}

The primary outcome is serum creatinine concentration. The secondary outcomes are IAP, measured creatinine clearance, daily urine output, the multiorgan disfunction score Chronic Liver Failure Sequential Organ Failure Assessment (CLIF-SOFA) [13] and the incidence of stage 3 acute kidney injury (AKI) (defined by Kidney Disease: Improving Global Outcomes—KDIGO AKI [29] score), as well as 28-day renal replacement therapy (RRT)-free days, 28-day survival rate, and ICU LOS. The outcomes variables will be assessed at day seven (D7) after randomization (D0), unless otherwise stated. Additionally, IAP, serum creatinine concentration, measured creatinine clearance, daily urine output, and CLIF-SOFA will be analyzed using their maximum or minimum and daily mean values between D1 and D7.

Whenever ICU discharge or liver transplant occurs before D7, the last available data prior to these events will be used for outcome assessment. Additionally, stage 3 AKI will be considered when RRT or death occurs and, in these circumstances, a serum creatinine concentration value of 4 mg/dL and creatinine clearance value of 10 mL/min will be used for outcome assessment as mentioned in the literature [13, 29, 30].

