## Assignment of interventions: allocation

### Sequence generation {16a}

The patient allocation method consists of stratified randomization with blocks within each subgroup. This method is particularly useful with randomizing small samples due to the ability to create balanced groups regarding predetermined variables or characteristics at the beginning of the trial, reducing differences in baseline trial groups characteristics’ that could harm later result analysis and conclusions.

In this small sample size trial, patients will be stratified according to maximum serum creatinine and maximum IAP, expected to be the two most important variables to balance between trial groups at baseline. Stratified randomization will homogenize trial groups ad initio to reduce the probability of unbalanced baseline group characteristics and biased results.

The stratification process will use two strata, namely, maximum IAP and maximum serum creatinine, thus creating four subgroups (I–IV): (I) IAP < 16 mmHg + serum creatinine < 1.5 mg/dL, (II) IAP < 16 mmHg + serum creatinine ≥ 1.5 mg/dL, (III) IAP ≥ 16 mmHg + serum creatinine < 1.5 mg/dL, and (IV) IAP ≥ 16 mmHg + serum creatinine ≥ 1.5 mg/dL [4, 13]. Each subgroup (I–IV) contains sequential blocks of randomized trial group allocation (A) control and (B) intervention, with a 1:1 ratio (i.e., *AABB*, *ABAB*, *BABA*, *BBAA*), as exemplified in Table 1.

**Table 1 Tab1:** Stratification subgroups (I-IV) created using maximum intra-abdominal pressure (IAP) and serum creatinine as strata. Example of stratified randomization with blocks within each subgroup (A, B)

Stratification subgroups (I–IV)	Creatinine < 1.5 mg/dL	Creatinine ≥ 1.5 mg/dL
IAP < 16 mmHg	I) ABAB, ABBA,…	III) BABA, BBAA,…
IAP ≥ 16 mmHg	II) BABA, AABB,…	IV) BBAA, BAAB,…

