Possible limitations in our trial protocol include the following: (1) underpowered sample size to identify significant differences for some secondary outcomes and paracentesis-related complications or harm; (2) reduced generalizability of results due to the single-center, specialized liver disease ICU setting; (3) selection bias due to the fixed block size randomization; for this reason, the group allocation will be revealed by the attending physician, rather than the P.I.; (4) clinical reasons may induce protocol non-adherence or violation, although this may reflect real-world conditions and improve generalizability of results.

Finally, we chose serum creatinine as the primary outcome variable to compare trial groups since it remains the most practical biomarker of renal function in patients with AKI [13]. Even though serum creatinine has some limitations, particularly regarding interpretation in the individual cirrhotic patient, the randomization process should homogenize patient characteristics at baseline and allow for the comparison of results between groups.

This research trial conforms with the ethical norms and standards in the Declaration of Helsinki, including local Ethics Committee (reference no. 632/2018, 11/02/2022) and registration (ClinicalTrials.gov NCT04322201). This trial has received internal funding granted from the Research Center (reference FFI 06/2019), exclusively for specific laboratory analysis described in the trial protocol.

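### The day-7 creatinine comparison leaves out baseline creatinine and both stratification factors, so the primary test is conservative and gives up precision that the trial's own data could supply.

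*Protocol article*

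**What the plan says.** Outcomes {12} of the protocol article states "The primary outcome is serum creatinine concentration" and adds "The outcomes variables will be assessed at day seven (D7) after randomization (D0), unless otherwise stated". Statistical methods {20a} then sets the form of the comparison: "Quantitative variables will be analyzed using the assessment day value (D7), the daily mean value, and their maximum or minimum values". For the test itself, a Mann–Whitney U "test will be used to compare study groups, assuming a non-normal distribution, or two independent sample" t-test. The sample size in section {14} rests on the same unadjusted two-sample t framework.

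Sequence generation {16a} stratifies the randomisation: "The stratification process will use two strata, namely, maximum IAP and maximum serum creatinine, thus creating four subgroups (I–IV"). The cut-points are 16 mmHg and 1.5 mg/dL, and these factors are "expected to be the two most important variables to balance between trial groups at baseline". The Discussion relies on this: "the randomization process should homogenize patient characteristics at baseline and allow for the comparison of results between groups".

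Some modelling is planned. Section {20a} says "Using daily values, mixed effects regression models will be used to consider the autocorrelation structure between the longitudinal measurements", and it promises univariable and multivariable versions of all regression studies to deal with potential confounders. It does not name baseline creatinine or the strata as covariates, and it does not make any of these models the primary analysis.

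**The concern.** Stratified blocks force the arms to be alike on the stratification factors, so the difference between arms varies less from trial to trial than under simple randomisation. A two-sample test does not know this. It leaves the variation between strata in its error term and behaves as if that variation could still fall unevenly between the arms. If the factors predict the outcome, the t-test's standard error is too large and both tests reject less often than their nominal level. The test also ignores what the exact baseline creatinine value says about day 7 beyond the 1.5 mg/dL split.

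What is at stake is precision in a trial of 70 patients, on the outcome that carries the conclusion. Creatinine and IAP must already be known before the envelope is opened, so using them needs no new data.

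**Working it through.** **1. The plan's own figure.** Inputs from Sample size {14}: difference 0.4 mg/dL, SDs 0.45 and 0.48, one-sided alpha 0.05, power 95%.
- Pooled SD = √((0.45² + 0.48²)/2) = 0.465, so the planned effect is 0.4/0.465 = 0.86 SD.
- The noncentral t gives 30 per arm, 60 in total. The stated 60 reproduces. Allowing for 15% attrition, 60/0.85 ≈ 71 and 60 × 1.15 = 69, which brackets the stated 70.

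**2. Assumption.** The correlation ρ between baseline and day-7 creatinine is not in the document. It is taken as 0.3, 0.5 and 0.7.

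**3. How far the unadjusted standard error is off.** Suppose the creatinine stratum splits a normal baseline at its median. It then carries a share 2/π = 0.637 of the baseline's predictive variance. With the strata fully balanced, true SD of the difference = reported SE × √(1 − 0.637ρ²), and actual two-sided error = 2 × [1 − Φ(1.96/√(1 − 0.637ρ²))].

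| ρ | √(1 − 0.637ρ²) | Actual error by formula |
|---|---|---|
| 0.3 | 0.971 | 4.4% |
| 0.5 | 0.917 | 3.3% |
| 0.7 | 0.829 | 1.8% |

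Simulation with 70 patients, four strata, blocks of 4, normal data and nominal two-sided 5% (4,000 trials per setting) agrees:

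| ρ | t-test | Mann–Whitney | ANCOVA with baseline and strata |
|---|---|---|---|
| 0.3 | 4.3% | 4.2% | 4.7% |
| 0.5 | 3.6% | 3.8% | 5.4% |
| 0.7 | 1.9% | 1.8% | 5.1% |

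The t-test reports a mean SE of 0.111 mg/dL against a true SD of about 0.108, 0.102 and 0.094. It is too large by about 3%, 9% and 18%.

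**4. Power, same simulation design, two-sided 5%.** Each cell gives t-test → ANCOVA.

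| Effect | ρ = 0.3 | ρ = 0.5 | ρ = 0.7 |
|---|---|---|---|
| 0.4 mg/dL, SD 0.465 (planned) | 94.6 → 95.7% | 95.6 → 98.2% | 97.2 → 99.9% |
| 0.3 mg/dL, SD 0.465 | 76 → 79% | 77 → 86% | 79 → 96% |
| 0.5 SD | 54 → 57% | 55 → 66% | 55 → 81% |
| 0.4 mg/dL, SD 1.2 (assumed) | 28 → 30% | 26 → 35% | 24 → 49% |

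At the planned effect the gain is 1.1, 2.6 and 2.8 points (from unrounded power). At 0.5 SD this run gives 3, 11 and 26 points; repeated runs put the last two at 11–12 and 26–28.

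**5. The block at 4 mg/dL.** Outcomes {12} assigns 4 mg/dL after RRT or death. The document does not say how many patients that will be, so the following shares are assumptions.
- *Baseline predicts the outcome well, a quarter to a third of patients at 4.* Mann–Whitney has 61% power against 72% for a rank-based adjusted analysis at ρ = 0.5, and 56% against 84% at ρ = 0.7.
- *Baseline only weakly predicts who gets the 4, 20–40% of patients at 4.* The realised correlation falls to about 0.3–0.4, and linear ANCOVA beats the t-test by only 1–3 points. Mann–Whitney then has far more power than linear ANCOVA (56% against 19–21% with 20% at 4).

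So with the block present, the gain depends on how strongly baseline predicts RRT or death, and a linear model alone is a poor replacement for a rank-type test.

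**The case against.** The strongest reply is that little is lost under the plan's own assumptions. That stands: at 0.4 mg/dL and SD 0.465, power is already near 95% and the gain is 1 to 3 points. The larger figures need an effect or SD that the plan does not state, and a correlation that it does not give.

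Second, a reader might infer that the plan contains no adjustment at all. It does: mixed models on daily values and multivariable regressions are promised, and a covariate list may properly sit in an analysis plan that is not shown. What remains is that the article fixes covariate-free tests for the day-7 comparison and leaves the adjusted models without primary status.

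Third, a reader might infer a biased estimate or a risk of false positive findings. Neither follows. Randomisation protects the estimate, and the error runs below 5%, not above it.

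Fourth, the choice between the two tests might be read as leaving the primary p-value open. The article does give a rule based on distribution between two named tests, and the criterion for normality is detail that an analysis plan can supply. No figure here shows harm from the switch, so it is secondary.

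Finally, which adjusted model to name is partly a matter of judgement. Mann–Whitney reports no standard error, so the point about over-wide intervals applies to the t-test only. A proportional-odds model gives no difference in mg/dL, the scale on which the target was set. The recommendation allows for both.

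**Conclusion.** The point holds as a recommendation on precision. The day-7 primary comparison ignores the variables that the trial itself treats as most important. With normal data and ρ of 0.3, 0.5 or 0.7, its actual two-sided error is about 4%, 3.5% or 2% where 5% is intended.

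The power cost is about 1 to 3 points at the planned effect. It rises to about 3, 11–12 and 26–28 points at 0.5 SD. A standardised effect below the planned 0.86 SD is plausible, since assigning 4 mg/dL after RRT or death is likely to widen the SD beyond 0.465.

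The direction is secure whenever the strata predict the outcome. The size is not: ρ, the SD with the assigned values and the share of patients at 4 mg/dL are all assumptions. The linear ANCOVA gains on normal data should not be credited to an ordinal or rank-based model. A reader might take the large gains as the loss under the trial's stated design, but the plan's own effect and SD do not support that.

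**What to change.** Name one primary analysis of day-7 creatinine, adjusted for baseline creatinine as a continuous variable and for the two stratification factors as randomised. Choose a form that tolerates the block at 4 mg/dL, for example proportional-odds regression or a rank-based covariate-adjusted analysis. Report an ANCOVA-adjusted difference in mg/dL with a 95% confidence interval beside it, to keep the scale of the sample-size target. Let this replace the distribution-driven choice between tests, and keep the unadjusted t-test and Mann–Whitney as sensitivity analyses.

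The cost is wording in the protocol or analysis plan; the covariates are already collected. Section {17a} leaves the data analysts unblinded, so the change should be dated and made before anyone examines creatinine by arm for this purpose.

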### Sample size {14}

The sample size was calculated using the statistical noncentral *t *function, with a one-sided alpha level of 0.05 [31]. The calculations were based on the expected renal function and IAP variation between groups, since we assume the former to be dependent of the latter.

To support the trial rationale of an expected clinically significant IAP decrease of 3 mmHg in the intervention group, a total of 44 patients are considered necessary to detect a statistically significant difference, with 1:1 allocation ratio, 80% statistical power, and 95% confidence level. This estimate is based in a post-hoc analysis of 61 patients with cirrhosis from a multicentric randomized controlled trial in shock patients where a mean difference in IAP of 3 mmHg was found between survivors and non-survivors (13.7 ± 3.9 and 16.7 ± 3.9 mmHg, respectively) [4].

Regarding the primary outcome, to detect a clinically and statistically significant decrease in serum creatinine of 0,4 mg/dL in the intervention group, a total of 60 patients is estimated, with a 1:1 allocation ratio, 95% statistical power, and 95% confidence. This estimate is based on a multicentric observational study of acutely decompensated patients with cirrhosis. In this study, cirrhotic acute-on-chronic liver failure patients with at least one organ failure had a mean creatinine difference of 0,4 mg/dL between survivors and non-survivor groups (0.9 ± 0.45 and 1.3 ± 0.48 mg/dL) [32].

We arbitrarily estimate that protocol non-adherence/attrition or violation after randomization may affect approximately 15% of cases and, therefore, to ensure that the number of patients that complete the protocol is reached for the primary outcome, the total sample size is set at 70 patients with a 1:1 group allocation ratio.

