## Data collection and management

### Plans for assessment and collection of outcomes {18a}

The assessment and collection of trial data will start at patient enrollment (D0) including vital signs, specific therapies (i.e., albumin, transfusions), vital organ support, blood, urine, and ascitic fluid tests, repeatedly up to D7.

The trial protocol includes the daily collection of an 8-h (480 min) urine volume, at blocked nocturnal interval from 23 to 07 h, for measurement of creatinine clearance, based on the following formula: creatinine clearance (mL/min) = (urinary creatinine [mg/mL] × urine volume [mL])/(serum creatinine [mg/mL] × urine collection time [480 min]) [34].

Daily blood analysis includes complete hemogram, coagulation, and biochemistry and arterial blood gas. Ascitic fluid will be collected with every new paracentesis and repeated every 48 h in the intervention group for screening of infectious complications.

Collected trial variables are mainly included in clinical severity scores APACHE II [35], SAPS II [36], CLIF-C ACLF [37], CLIF-SOFA, SOFA [38], RIFLE [30], KDIGO [29], ICA-AKI [13], MELD [39], and MELD-Na [40] and incorporate liver disease etiology, precipitant event for critical illness, urine output, serum creatinine, estimated and measured creatinine clearance, and number of days on RRT, Glasgow coma score and West-Haven scale, number of days under vasopressor support and dosage, PaO_2_/FiO_2_ ratio, positive end-expiratory pressure and number of days under mechanical ventilation, total bilirubin, coagulation international normalized ratio, platelet count, arterial blood lactate and prescribed albumin dosage. Intermediate effect variables IAP and APP will be measured throughout ICU stay to test the trial rationale.

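### 28-day RRT-free days is a day count, but the only analysis assigned to it is a competing-risks survival model, which does not estimate that count or use the days on RRT

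*Protocol article*

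**What the plan says.** Protocol article, Outcomes {12}, lists among the secondary outcomes "as well as 28-day renal replacement therapy (RRT)-free days, 28-day survival rate, and ICU LOS". RRT-free days is thus a number between 0 and 28 for each patient.

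Statistical methods {20a} gives this outcome one sentence of its own: "For the study of RRT-free days, competing risks survival models will be applied considering death as the competing risk". It names neither the event of interest nor the class of model (cause-specific or subdistribution).

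Plans for assessment and collection {18a} includes RRT duration among the collected variables: "number of days on RRT, Glasgow coma score and West-Haven scale".

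Outcomes {12} also states how death is scored for other renal outcomes: "stage 3 AKI will be considered when RRT or death occurs", with fixed values of 4 mg/dL for creatinine and 10 mL/min for clearance in the same circumstances. It gives no such rule for RRT-free days.

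**The concern.** A competing-risks model needs an event and a time to it. If death is the competing event, the event of interest can hardly be anything but the start of RRT. The model then describes whether and when RRT begins, whereas the outcome describes how many of 28 days were free of it. Two things follow.

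- **Duration drops out.** A patient on RRT for 3 days and one on it for 14 days contribute the same information if they started on the same day. A benefit through shorter RRT would not be seen.
- **Death is not counted as a bad result.** It removes the patient from the chance of RRT. If the effect is read on the cumulative-incidence scale, an arm with more early deaths has fewer patients left to start RRT and can appear better.

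At stake is whether the result reported as RRT-free days answers the question that its name poses. The primary outcome is not involved.

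**Working it through.** The protocol gives no expected RRT rate, mortality or RRT duration for this trial, so there is no figure of its own to reproduce. All rates below are assumptions, chosen to show direction and rough size.

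**Set-up.** Constant hazards per day: r for starting RRT and d for death, with death unaffected by RRT; one RRT spell of fixed length m days; follow-up of 28 days.

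- Cumulative incidence of RRT: r/(r+d) × (1 − e^(−28(r+d)))
- 28-day mortality: 1 − e^(−28d)
- Mean days on RRT in a 28-day survivor: m − (e^(−r(28−m)) − e^(−28r))/r
- Mean RRT-free days with death scored 0: e^(−28d) × (28 − mean days on RRT in a survivor)

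**1. Deaths differ, RRT hazard equal** (r = 0.02; d = 0.01 v 0.03; m = 7)

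- RRT incidence: 0.02/0.03 × (1 − e^(−0.84)) = 0.379; 0.02/0.05 × (1 − e^(−1.4)) = 0.301.
- Mortality: 1 − e^(−0.28) = 24%; 1 − e^(−0.84) = 57%.
- Cause-specific hazard ratio: 0.02/0.02 = 1.
- Days on RRT in a survivor: 7 − (e^(−0.42) − e^(−0.56))/0.02 = 7 − 4.29 = 2.71.
- RRT-free days with death = 0: 0.756 × 25.29 = 19.1; 0.432 × 25.29 = 10.9.

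On the incidence scale the arm with 57% mortality looks better (30% v 38%). On the day count it is worse by 8.2 days. The cause-specific hazard shows no difference.

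**2. RRT duration differs, hazards equal** (r = d = 0.02; m = 4 v 14)

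- RRT incidence is the same in both arms, because m does not enter the formula: 0.02/0.04 × (1 − e^(−1.12)) = 0.337. Both kinds of hazard ratio are 1.
- RRT-free days with death = 0: 0.571 × (28 − 1.62) = 15.1; 0.571 × (28 − 4.77) = 13.3.

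**3. Range.** Hold the RRT hazard at the level that gives 40% RRT by day 28 in the absence of death, and vary 28-day mortality:

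| 28-day mortality | 20% | 30% | 40% | 50% | 60% | 70% |
|---|---|---|---|---|---|---|
| RRT incidence | 36.2% | 34.2% | 32.0% | 29.7% | 27.2% | 24.4% |

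At a fixed RRT hazard, more death always lowers RRT incidence; the size depends on the assumed rates.

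**4. At the trial's size.** The plan is "the total sample size is set at 70 patients with a 1:1 group allocation ratio", that is 35 per arm. Simulation with the same RRT hazard and RRT spells of random length (exponential, mean 7 days in both arms) gave:

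| 28-day mortality | Fine-Gray ratio | Cause-specific ratio | RRT-free days, death = 0 |
|---|---|---|---|
| 30% v 60% | 0.77 | 1.00 | 18.1 v 10.3 |
| 40% v 60% | 0.83 | 0.99 | 15.5 v 10.4 |

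Ratios below 1 favour the arm with more deaths. In 3,000 simulated trials at 30% v 60%, the Fine-Gray estimate favoured that arm in 72% and reached two-sided significance at 0.05 in 8%. A Mann-Whitney test of the count with death = 0 rejected in 65%, against the arm with more deaths. With equal hazards (40% mortality) and mean RRT duration 14 v 3 days, both hazard ratios were 0.99, while days alive and free of RRT were 19.4 v 21.1.

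**The case against.** - **The event is not stated.** Correct: time to first RRT is an inference. It is the natural reading of a model with death as the competing risk, and no other event in the text fits better, but it should be put as an inference.
- **A reader might infer that the planned analysis will reward the arm with more deaths.** The document does not support that. The distortion arises with cumulative incidence or a Fine-Gray model; a cause-specific hazard is neutral in the same scenario. The protocol chooses neither, and the choice may properly sit in an analysis plan that is not shown. Even under Fine-Gray, a significant false advantage was uncommon at 35 per arm. What stands is that neither class counts deaths against an arm and neither uses RRT duration.
- **A reader might also infer that the protocol requires death to be scored as 0 days.** It does not. That is a convention, and it contributes to the size shown. Counting actual days alive without RRT in the first example gives 24.42 − 2.34 = 22.1 v 18.94 − 1.78 = 17.2, a gap of 4.9 days instead of 8.2. The direction is unchanged.
- **The general test sentence may cover the count.** The Mann-Whitney and t-test sentence in Statistical methods {20a} follows one about D7 values, daily means and maxima or minima. RRT-free days runs to day 28 and has its own sentence, so the general one does not clearly apply.
- **Mortality is reported anyway.** True: 28-day survival is a separate outcome, so an imbalance would be visible. That limits the harm but does not make the model fit the outcome.

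**Conclusion.** The point holds as a mismatch between a stated outcome and the analysis stated for it, not as missing detail. On the natural reading, the model estimates something other than RRT-free days and leaves out the days on RRT; this does not depend on the model class or on any assumed rate.

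The second effect is conditional. If cumulative incidence or Fine-Gray is used and mortality differs between arms, the result can favour the arm with more deaths: 38% v 30% RRT incidence at 24% v 57% mortality under the assumed hazards. That illustration uses a wide mortality gap and equal RRT hazards, neither of which comes from the protocol. With a cause-specific hazard the comparison is neutral.

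The outcome is secondary, so the primary conclusion is unaffected. The correction is worth making before analysis because it changes what is estimated.

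**What to change.** 1. In Statistical methods {20a}, analyse 28-day RRT-free days as a count, by a rank test or a proportional-odds model that includes the randomisation strata (maximum IAP and maximum serum creatinine).
2. In Outcomes {12}, state the rule for death by day 28. Scoring it as 0 days is one option, in line with that section's treatment of death as an adverse renal result for creatinine, clearance and stage 3 AKI.
3. Keep the competing-risks model for a separately named supportive outcome, time to first RRT. Name the event and the model class, and report it beside 28-day mortality.

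The cost is wording: days on RRT are already collected, though it should be confirmed that they are recorded to day 28. The drawback is that scoring death as 0 makes the count partly a mortality composite, so its components (deaths, patients receiving RRT, days on RRT) should be shown by arm.

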## Trial hypothesis

A continuous passive paracentesis (CPP) strategy in the treatment of IAH improves organ dysfunction and clinical outcomes when compared to standard LVP in the critically ill cirrhotic with ascites.

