## Interventions

### Explanation for the choice of comparators {6b}

This trial compares two methods of therapeutic paracentesis, namely, CPP versus standard-of-care LVP in the prevention and treatment of IAH. The CPP is expected to improve ascitic fluid drainage, therefore, providing better prevention and treatment of IAH, rather than intermittent LVP, which allows for the periodical accumulation of ascites with the potential deleterious effects of intermittent increases of IAP.

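### The only method named for time until death is a joint model whose usual CPP coefficient is a direct effect, so a treatment-only comparison should be stated beside it

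*Protocol article*

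**What the plan says.** - **Time until death.** The section on statistical methods for primary and secondary outcomes {20a} states: "Regarding time until death, joint survival regression models will be used to take into consideration the association of longitudinal markers with time until death". It gives no other method specifically for time until death. It does not name the markers or say which quantity from the model will be reported as the effect of CPP.
- **Hypothesis.** CPP "improves organ dysfunction and clinical outcomes when compared to standard LVP in the critically ill cirrhotic with ascites". This contrasts the two randomised strategies as wholes.
- **Mechanism.** Under the choice of comparators {6b}: "The CPP is expected to improve ascitic fluid drainage, therefore, providing better prevention and treatment of IAH". Under data collection {18a}: "Intermediate effect variables IAP and APP will be measured throughout ICU stay to test the trial rationale". Under sample size {14}: "The calculations were based on the expected renal function and IAP variation between groups, since we assume the former to be dependent of the latter".
- **Mortality outcome.** The outcomes section {12} lists "28-day survival rate, and ICU LOS" among the secondary outcomes, so the declared mortality measure is a proportion. For such variables {20a} says: "Dichotomous categorical variables will be analyzed using chi-square or Fisher’s exact tests".
- **Regressions in general.** "For all regression studies, univariable and multivariable analyses will be performed to account for potential confounders".

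**The concern.** A joint model links a longitudinal marker to the hazard of death. If the marker lies on the path from treatment to death, the treatment term left in the hazard describes only what treatment does at a given marker path. The daily series that the trial collects (IAP, creatinine, creatinine clearance, urine output, CLIF-SOFA) are all measured after randomisation, and by the protocol's own reasoning they lie on or downstream of that path.

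The time-to-death hazard ratio could then mislead in two ways. If CPP saves lives by lowering IAP, it could sit near 1 and be read as no effect on survival. If CPP lowers IAP but does harm by another route, with no net change in deaths, it could point to harm. The Discussion itself names infection and abdominal wall fistula as possible added risks of CPP.

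**Working it through.** **1. Plan's own figures.** The protocol gives no figure for mortality or time to death. The figures borrowed below come from the sample size section, which reproduces: with a noncentral t, one-sided alpha 0.05 and 1:1 allocation, 3 mmHg with SD 3.9 at 80% power gives 44 patients, and 0.4 mg/dL with pooled SD √((0.45² + 0.48²)/2) = 0.465 at 95% power gives 60.

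**2. What the coefficient means.** In the usual form the hazard is h(t) = h0(t) · exp(γ·CPP + α·m(t)), where m(t) is the patient's current marker value. If CPP shifts the marker by β, then:
- conditional (direct) log hazard ratio = γ
- overall log hazard ratio = γ + α·β

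The hypothesis concerns the second. A test of γ = 0 addresses the first.

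**3. Size of α·β implied by the sample size section.** The survivor versus non-survivor differences are converted to a slope as difference/SD². Strictly this is a log odds; it is used here as a log hazard.
- IAP: 3/3.9² = 0.197 per mmHg; for 3 mmHg, 0.592; exp(−0.592) = 0.55.
- Creatinine: 0.4/0.465² = 1.85 per mg/dL; for 0.4 mg/dL, 0.74; exp(−0.74) = 0.48.

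**4. Fully mediated benefit (γ = 0), IAP path.** CPP lowers IAP by 3 mmHg (SD 3.9). IAP is held constant to day 28 and entered directly without error, as a simple stand-in for the survival part of a joint model. Daily control hazards of 0.01, 0.02 and 0.03 at the mean control IAP set the assumed mortality.

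Large sample (20,000 patients):

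| 28-day mortality, control / CPP | CPP HR, no marker | CPP HR given IAP | Overall HR from the marker model |
|---|---|---|---|
| 28.1% / 17.1% | 0.57 | 1.01 | 0.55 |
| 46.0% / 29.7% | 0.57 | 0.98 | 0.54 |
| 56.7% / 40.7% | 0.62 | 1.00 | 0.55 |

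Trial size (70 patients, 1,000 simulated trials per row, two-sided 0.05), rejection rates:

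| 28-day mortality, control / CPP | Cox, CPP only | CPP term given IAP | Chi-square on 28-day mortality |
|---|---|---|---|
| 28.2% / 17.8% | 16.7% | 5.5% | 18.5% |
| 45.9% / 30.4% | 25.3% | 5.4% | 26.5% |
| 57.0% / 40.4% | 29.8% | 4.9% | 27.2% |

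The conditional term rejects at about the rate expected under no effect. The planned chi-square test keeps the total effect.

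**5. Partial mediation.** If half of the 0.592 runs through IAP, the conditional hazard ratio is exp(−0.296) = 0.74 against an overall exp(−0.592) = 0.55. The gap shrinks but does not close.

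**6. Marker benefit cancelled by direct harm.** Setting γ = −α·β gives a conditional hazard ratio of exp(0.592) = 1.81 (IAP) or exp(0.74) = 2.10 (creatinine) with equal deaths in both arms. At 70 patients with an immediate, constant marker shift, the conditional term rejects in 42% to 59% of trials (creatinine, assumed mortality 40% to 60%) or 30% to 37% (IAP, 40% to 50%); Cox with arm alone rejects in 3% to 7%. If the shift builds up linearly to day 7, the conditional term rejects in 39% and 28% at 50% mortality, and Cox in about 5%.

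**The case against.** A reader might infer that the plan tests mortality only through the conditional coefficient and so loses any survival benefit that works through IAP or creatinine. The document does not support that, for four reasons.

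- **The declared outcome is tested elsewhere.** The listed mortality outcome is the 28-day survival rate, and the rule for dichotomous variables compares the randomised groups with no post-randomisation marker. This stands, and it refutes the broad reading.
- **The model can give the overall effect.** γ + α·β can be reported from a joint model, and {20a} does not say that γ alone will be tested. The markers and the tested contrast are inferences, and such detail could be in an analysis plan that is not shown. This stands, but the text as published does not point to the overall effect.
- **The joint model serves another aim.** The general objective {7} is to assess the impact of intra-abdominal hypertension on outcomes, and the association parameter speaks to that. This is a good reason to keep the model, though not to take the CPP effect on survival time from it.
- **Univariable analyses are promised.** These might include a model for death by arm alone. But a joint model contains a marker by construction, so how the rule applies is unclear, and a mediator is not a confounder to be adjusted for.

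The simulated sizes are also open to challenge. They assume control mortality, treat cross-sectional survivor differences as causal, give the model an error-free marker to day 28 although protocol measurements run to day 7, and in step 6 use a harm chosen to cancel the benefit exactly.

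**Conclusion.** The point holds in a limited form. The one method named for time until death does not, in its usual form, target the total effect of CPP in the trial hypothesis. Under a fully IAP-mediated benefit its CPP hazard ratio would centre near 1 (0.98 to 1.01) where the marker-free value is 0.57 to 0.62. Under exactly offsetting harm it could suggest excess mortality when deaths are equal. The direction follows from the model; the size depends on assumed mortality and on how much of the effect is mediated.

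The 28-day survival comparison is unaffected, as are the primary outcome and the sample size. Power for mortality is low by any route: 17% to 30% for the treatment-only Cox model in step 4. The practical risk is two mortality results that answer different questions, with no statement of which one represents the effect of CPP. This is a cheap improvement to a secondary analysis.

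**What to change.** In {20a}, replace the sentence on time until death with wording such as:

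> The treatment effect on time to death up to day 28 will be estimated by a Cox model with randomised group, the stratification factors (maximum IAP and maximum creatinine before randomisation) and baseline values only; no post-randomisation marker enters this model. Joint models of longitudinal markers and death are secondary and explanatory, describing the marker–death association. If a treatment effect is reported from a joint model, it will be the overall effect (direct plus marker-mediated), not the conditional coefficient alone.

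Keep the baseline terms few: the step 4 scenarios imply only about 35 × (0.282 + 0.178) = 16 to 35 × (0.570 + 0.404) = 34 deaths.

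The cost is a change of wording and one additional simple model. No further patients or data are needed, and the joint model is kept for the general objective.
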